**Fig 2 pone.0260828.g002:**
[figure not shown]
Flowchart of study procedures.

#### The dayzz app

The dayzz app is a personalized, digital sleep assessment and treatment program offered via smartphone. The dayzz app begins with a brief onboarding and registration process, followed by the administration of a clinically validated digital sleep disorders questionnaire (DSQ) [16]. The DSQ uses machine learning algorithms, previously validated against gold-standard physician sleep diagnoses, to identify people at high risk for four common sleep conditions: insomnia, delayed sleep phase syndrome (DSPS), insufficient sleep syndrome (ISS), and suspected obstructive sleep apnea. The information regarding sleep disorders is used to best tailor the sleep training plan and track progress for each individual user.

During the onboarding process, the user has the option to connect an external sleep monitor (e.g., Fitbit, Garmin, Whithings, Oura, Apple Watch) or a digital health data platform (e.g., Apple Health) and permit dayzz to stream live sleep and activity data into the app and prepopulate nightly sleep trackers. Users who do not connect wearable devices can manually enter daily sleep data using the app’s sleep tracker feature. Users can also enter sleep information retroactively and can override wearable sleep data by manually editing their sleep information within the sleep tracker feature. Users can review their sleep progress over time within the app as well, using a range of features reflecting the user’s sleep and progress during the sleep training.

Based on the user’s sleep assessment outcomes, behavioral data, and collected sleep data (subjective and/or objective), the dayzz app offers the user a personalized sleep training and improvement plan. Training plans consist of modules aimed at improving the user’s specific sleep issues. Modules are tailored to deliver evidence-based therapies for the specific sleep issue users report, for example, cognitive-behavioral skills and strategies for users at risk for insomnia. All users are provided with modules covering basic sleep hygiene principles and tools, such as bedroom environment optimization (integrating smartphone noise and light sensors), white noise audios, and written or auditory content to promote sleep health.

In addition, for users identified with suspected sleep apnea syndrome, a unique module was designed specifically for the purposes of this study, which recommends the user may benefit from a more in-depth sleep evaluation by a sleep physician. The module offers users the option to voluntarily set up visits (virtual or in-person) at a local sleep center for further evaluation (including home sleep studies per the doctor’s referral), track their progress (non-medical), and remind them of their scheduled appointments. Individuals diagnosed with Obstructive Sleep Apnea and prescribed a Continuous Positive Airway Pressure (CPAP) device by the physician, will be offered a training module to support the adjustment and adherence to their CPAP treatment.

To encourage user engagement with the dayzz app and increase adherence to intervention modules, the platform integrates contextual coaching strategies in the form of real-time intervention prompts to encourage positive sleep health-related behaviors and adherence to the training program. Such prompts include push notifications, chat messages, in-app overlays and email messages providing individual sleep feedback and task recommendations, sleep knowledge, rewards in the forms of badges for sleep-related behavioral change efforts and sleep metric achievements. The timing of the prompts is optimized for each individual user and based on smartphone sensor data, including location (GPS, WiFi connectivity), movement (accelerometer), time of day, and smartphone active/idle time. Users are asked but are not required to accept app permissions, such as location, motion, and fitness data access, to provide an enhanced user experience.

### Measures

We will describe the feasibility and acceptability of the app, and evaluate changes in sleep, health, safety, healthcare utilization, and workplace outcomes using self-reported questionnaires.

#### Feasibility and acceptability of the app

We will collect feasibility and acceptability data in the experimental group only, using two ways. First, participants in the experimental group will provide subjective ratings of acceptability of the app on the end-of-study questionnaire. Specifically, participants will be asked to respond to several questions, including “Did the study app provide helpful information?,” “Would you recommend the app to others?” and “Did you find the app easy to use?” Responses will be collected on scales from 1 (“Not at all helpful or “Not at all”) to 7 (“Very helpful” or “Very much so”). Second, we will collect objective app usage data provided by the developers, including: a) number of modules and tasks within each module completed on the app, per participant; b) number of features utilized, such as embedded apps (e.g. Spotify), reminders (e.g., last cup of coffee, alarm), use of favorites gallery); c) use of the chat option; d) responsiveness to notifications; f) number of achievements/badges received for reaching predefined goals; g) number of days and times the app is accessed; and h) integration of wearable devices; to characterize engagement with the intervention.

#### Changes in sleep behavior

We will evaluate changes in sleep behaviors on the monthly and the end-of-study surveys. Using a checklist, participants will be asked to select the healthy sleep changes they have made since starting the study. Specifically, participants are asked “During this study, have you changed any sleep-related behaviors to improve your sleep since participating in the study (check all that apply)?” Participants have the option to select changes they may have made, such as “Go to bed earlier,” “Keep a more consistent sleeping schedule,” and “Set an alarm to remind you of your bedtime.” Participants are also able to select “other” and identify the healthy sleep change they made since joining the study.

#### Sleep duration and regularity

Participants will self-report their sleep duration and timing on the eDiary. The Sleep Regularity Index is the percentage probability of an individual being in the same state (asleep vs. awake) at any two time-points 24 h apart, averaged across the study [17]. The index is scaled so that an individual who sleeps and wakes at exactly the same times each day scores 100 (better outcome), whereas an individual who sleeps and wakes at random scores 0 (worse outcome).

#### Sleep quality

Sleep quality will be measured using the Pittsburgh Sleep Quality Index (PSQI) [18]. The Pittsburgh Sleep Quality Index (PSQI) is an effective instrument used to measure the quality and patterns of sleep in adults. It differentiates "poor" from "good" sleep by measuring seven domains: subjective sleep quality, sleep latency, sleep duration, habitual sleep efficiency, sleep disturbances, use of sleep medication, and daytime dysfunction over the last month. The participant self-rates each of these seven areas of sleep. Scoring of the answers is based on a 0 to 3 scale, whereby 3 reflects the negative extreme on the Likert scale. Global scores range from 0–21 with a score of 5 or greater indicating poor sleep.

#### Workplace absenteeism, performance, and productivity

Absenteeism, performance, and productivity will be evaluated on the monthly questionnaire using the World Health Organization (WHO) Health and Work Performance Questionnaire Short Form [19]. Participants will be asked the number of hours worked in a typical week. Unscheduled absences and disability day usage will be collected by self-report. Presenteeism questions ask the worker to compare both their performance to their best possible performance, and separately, their performance to the performance of most workers in a similar job. A ratio of workplace performance relative to ideal or possible performance will be calculated. Absenteeism and presenteeism can be converted to workplace cost by multiplying the number of hours lost by the individuals’ salary, which is reported on the demographic questionnaire.

#### Mood, alertness, and energy

Mood, alertness, and energy will be assessed on the eDiary. Specifically, participants will be asked to report, using 100 mm visual analog scales, their: 1) mood from "Sad" (0) to "Happy" (100); their 2) alertness from "Sleepy" (0) to "Alert" (100); and 3) energy from “Sluggish" (0) to "Energetic" (100). Higher scores indicate a better outcome. On the monthly questionnaires, we will also assess mood on a 7-point scale from “Very poor” (0) to “Very good” (7), alertness from “Very poor” (0) to “Very good” (7) and energy from “Very low” to “Very high” (7).

#### Adverse health and safety outcomes

Motor vehicle crashes and near-crashes will be captured via self-report on the monthly questionnaire, consistent with previous studies [7,20]. Participants will be asked, “In the last month, did you have any motor vehicle accidents or crashes (actual collisions) in which you were driving,” and “In the last month, did you have any near miss motor vehicle accidents or crashes (narrowly avoided property damage or bodily harm) in which you were driving.” Participants who responded yes will then be asked to provide the number of times that each outcome occurred during the month. We will also assess injuries by asking participants “In the last month, how many injuries did you have” and attentional failures by asking participants the number of times they “Nod off or fall asleep during meetings at work,” “…on the telephone,” “…while driving,” and “…while stopped in traffic.”

#### Healthcare utilization

Healthcare utilization will be reported on monthly surveys. Participants will be asked to report interaction with the healthcare system, including visits to their primary care provider, emergency room, urgent care, or a specialist. They will further be asked to report any laboratory tests and diagnostic evaluations, including imaging, home sleep tests, and other examples of healthcare utilization. Healthcare costs will be estimated for each interaction through applying national average costs for each visit, test, and/or procedure.

### Power analysis

The power analysis was performed on the anticipated cohort of 1000 active participants providing adequate data for comparison (500 in each arm of the protocol). Power was estimated for each of the aims using GPower version 3.1.9.4. We will be able to detect slightly smaller effects for continuous variables compared to binary variables if we choose to dichotomize in the analysis (e.g. any motor vehicle crash vs. none). A sample size of 500 in each group will enable us to detect an effect size of 0.16 between the groups (even if the impact is small, we will be able to detect a significant difference). This effect size roughly translates to a relative risk of 1.20. If fewer participants enroll than we expect, we will still be able to detect a small difference in effect size if we enroll at least 600 participants.

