## Materials and methods

### Study design

We will conduct a single-site, randomized, two-arm, parallel-group controlled trial using a waitlist control design. We will enroll a target of 1,000 daytime employees into the study, 500 randomly assigned to the experimental group and 500 to the control group. The experimental group will receive access to the dayzz app as well as to a short sleep health and wellness (SHAW) education program, developed by the Sleep Matters Initiative which includes screening for common sleep disorders. The control group will receive the dayzz app and SHAW at the end of the study. The study recruitment was originally intended to be conducted in-person. However, due to the onset of the COVID-19 pandemic at the start of study implementation, the study recruitment, enrollment, and follow-up procedures were re-designed to be completed entirely online. Please see the Fig 1 for a flowchart of enrollment, interventions, and assessments.

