### Statistical plan

We plan to analyze anonymized data using an intention-to-treat approach (ITT). All outcome measures will be compared by assignment to the experimental and waitlist control groups in the primary analysis. The primary ITT analysis will include all participants who are randomized in the study. Secondary analyses will compare outcomes using an as-treated approach and an adherent to treatment approach. The as-treated approach will compare those who download dayzz to those who do not, regardless of their assigned randomization. We anticipate some cross-over between groups due to sharing of the app information among study participants. The adherent to treatment approach will exclude participants from the experimental group who did not engage with app throughout the study. We further plan to quantify temporal changes within participants assigned to the experimental group.

To evaluate changes in sleep behavior, we will examine the distribution of the data to determine if it meets assumptions for parametric tests. Assuming randomization has balanced known and unknown confounders and we observe a normal distribution, we will compare sleep duration between the groups using a t-test. We will use a rank sum test if the distribution is not normal. The distribution of the data will be examined, and transformations will be performed as necessary for valid comparisons. If potential confounders are not balanced between groups, we plan to use regression models with an appropriate link function and distribution to test all hypotheses. The number of healthy sleep changes at the end of the study will be compared between the groups using a rank sum test.

To evaluate changes in sleep quality, we will compare the proportion of participants with poor sleep quality according to the PSQI in the experimental group versus the waitlist control group using a chi-2 test. These continuous measures will be compared using a t-test. To examine changes in mood, alertness, and energy we will compare these ordinal variables using Wilcoxon rank sum tests between the experimental and waitlist control arms. We will estimate changes in absences and productivity using reported salary information and compare the cumulative cost of each using a t-test. We will estimate the incidence of crashes, near-crashes, and injuries which will then be compared using Poisson regression. Finally, we will compare cumulative healthcare costs over the study using t-tests.

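### The power statement promises more sensitivity than the design has: relative risk 1.20 fits only outcomes near 40% risk, no loss of data is allowed for, and 0.16 rests on an undeclared test convention

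*Protocol article*

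**What the plan says.** The Power analysis section of the protocol article starts from this base: "The power analysis was performed on the anticipated cohort of 1000 active participants providing adequate data for comparison". The Study design section sets recruitment at the same number: "We will enroll a target of 1,000 daytime employees into the study", split 500 and 500.

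The Power analysis section then states: "A sample size of 500 in each group will enable us to detect an effect size of 0.16 between the groups", and adds: "This effect size roughly translates to a relative risk of 1.20". It assures the reader that even a small impact would be detected. It gives no control event rate, alpha, sidedness or power, and says only: "Power was estimated for each of the aims using GPower version 3.1.9.4". Its one example of a binary outcome comes where it discusses what happens "if we choose to dichotomize in the analysis (e.g. any motor vehicle crash vs. none"). A fallback of at least 600 participants is also expressed as a number enrolled.

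The Statistical plan section names t-tests, rank sum tests, a chi-square comparison of poor sleep on the PSQI, and Poisson regression for crashes, near-crashes and injuries. It declares no one-sided test.

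**The concern.** A standardised effect size does not convert to one relative risk. The conversion depends on the control risk, and for rare events a fixed effect size corresponds to a much larger relative risk. Quoting RR 1.20 with no event rate, next to a crash example, invites the reader to think that a 20% relative difference in crashes is within reach.

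Using one figure for both enrolled and analysable participants means that the calculation assumes complete data. Follow-up is entirely online, by emailed questionnaires, for up to 9 months.

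The figure 0.16 is also smaller than a conventional two-sided calculation gives for 500 per arm.

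At stake is how a null result is read. If crashes do not differ between arms, a reader relying on this paragraph could take that as evidence against a modest effect, when the trial could not have seen one.

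**Working it through.** **Inputs.** From the protocol article: 500 per arm, effect size 0.16, RR 1.20, enrolment target 1,000, follow-up up to 9 months. Assumed, because not stated: alpha 5%, power 80%, crash risks of 1% to 10% over follow-up, and data loss of 20% or 30%. Equal arms are used; a 1.3 to 1 split of 1,000 moves the two-sided result below only from 0.177 to 0.179.

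**Step 1. Reproduce 0.16.** For a two-sample t-test, detectable d ≈ (z for alpha + z for power) × √(2/n), and √(2/500) = 0.06325. Noncentral t agrees with each result to within 0.001.

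- One-sided 5%, 80% power: (1.645 + 0.842) × 0.06325 = 0.157
- Two-sided 10%, 80% power: the same, 0.157
- Two-sided 5%, 70% power: (1.960 + 0.524) × 0.06325 = 0.157
- Two-sided 5%, 80% power: (1.960 + 0.842) × 0.06325 = 0.177

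The first three round to 0.16; the last rounds to 0.18. Two-sided power at 0.16 is Φ(0.16/0.06325 − 1.960) = Φ(0.570), or 71.5% with noncentral t. About 614 per arm would be needed for 80%.

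**Step 2. Allow for missing data.** The same formulas with fewer analysable participants:

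| Assumed loss | Analysable per arm | Detectable d, two-sided | Power at 0.16, two-sided | Power at 0.16, one-sided |
|---|---|---|---|---|
| 0% | 500 | 0.177 | 71.5% | 81% |
| 20% | 400 | 0.198 | 62% | 73% |
| 30% | 350 | 0.212 | 56% | 68% |

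**Step 3. Convert 0.16 to a relative risk.** For proportions, h = 2·arcsin√(1.2p) − 2·arcsin√p, where p is the lower-arm risk. Setting h = 0.16 gives p = 0.396. At p = 1%, 5% and 10%, RR 1.20 corresponds to h = 0.019, 0.044 and 0.064, far below 0.16.

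**Step 4. Power for RR 1.20.** Pooled two-proportion test, two-sided 5%: power = Φ[(|p₁ − p₂| − 1.960 × SE₀)/SE₁], with SE₀ from the pooled risk and SE₁ from the separate risks. Example at 5% versus 6%: SE₀ and SE₁ are both 0.0144, so power = Φ[(0.01 − 0.0283)/0.0144] = Φ(−1.27) = 10%.

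| Control risk | Power for RR 1.20, 500 per arm | RR detectable at 80% power | n per arm for RR 1.20 |
|---|---|---|---|
| 1% | 5% | 3.7 | 42,693 |
| 2% | 6% | 2.7 | 21,109 |
| 5% | 10% | 1.9 | 8,158 |
| 10% | 17% | 1.6 | 3,841 |
| 20% | 33% | 1.4 | 1,683 |
| 40% | 72% | 1.22 | 604 |

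In the protective direction, the one the intervention aims at, the detectable RR is 0.53 at a 10% control risk and 0.36 at 5%. At 1%, even removing every crash would not reach 80% power.

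**Step 5. Check against the planned Poisson analysis.** Treating the rate ratio approximately, total events = 4 × (1.960 + 0.842)² / (ln 1.2)² = 4 × 7.849 / 0.03324 ≈ 945 (744 one-sided). With 1,000 participants that is close to one crash each within 9 months. The switch from proportions to rates does not rescue RR 1.20.

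**The case against.** The strongest reply is that the article states no alpha, sidedness or power, so a reviewer who supplies two-sided 5% and 80% and then finds a mismatch has not shown an error. That stands. A reader might infer that 0.16 is an arithmetic mistake, or that it can come only from a one-sided test. The documents support neither: Step 1 reproduces it under three conventions. The missing settings may also sit in a fuller document. What remains is that the natural reading of the named tests, such as the comparison of poor sleep "in the experimental group versus the waitlist control group using a chi-2 test", is two-sided, and on that reading 0.16 is too favourable.

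Second, the conversion is described as rough, and the crash example stands in a different sentence. RR 1.20 is reasonable for an outcome near 40%, which poor sleep on the PSQI may be; the Introduction cites 30–40% of employees screening positive for a sleep disorder. That also stands, but the paragraph does not limit the RR to such outcomes, and its only binary example is crashes.

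Third, the claim that continuous outcomes allow only slightly smaller detectable effects is defensible on the effect-size scale. It misleads only when read as relative risk.

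Fourth, the paragraph openly refers to people with adequate data, provides a 600 fallback, and the article describes incentives and reminders. The loss rates used here are assumptions. Still, the fallback counts people enrolled, so it does not address missing data, and incentives do not justify assuming complete data.

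Finally, a reader might extend the crash result to near-crashes and injuries. The documents give no rates for these, so that step is unsupported.

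**Conclusion.** The concern holds in a limited form. The clearest fault does not depend on sidedness: RR 1.20 corresponds to 0.16 only near a 40% control risk. The crash figures rest on assumed risks of 1% to 10%, but the conclusion is robust, because roughly two in five participants would have to crash within 9 months for the equivalence to apply.

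The second fault is that zero loss is built in. At an assumed 20% loss, 0.16 misses 80% power on either reading of sidedness.

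The third is one of disclosure: 0.16 is reproducible but belongs to a convention that the article does not declare, and the conventional two-sided figure is 0.18. That difference is small in itself. Nothing here shows that the trial is too small for its continuous sleep outcomes; the fault is in what the paragraph claims.

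**What to change.** Rewrite the Power analysis paragraph and leave enrolment as it is:

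- State alpha, sidedness and power. Either give the detectable standardised difference as 0.18 (two-sided 5%, 80% power, 500 analysable per arm), or declare and justify a one-sided test.
- Separate enrolled from analysable numbers and give the detectable difference under stated loss rates: for example 0.20 with 20% and 0.21 with 30% lacking data. Express the 600 fallback in analysable participants too.
- Replace the single RR 1.20 with detectable RRs by control risk, as tabulated above. Note that about 1.20 applies only to outcomes near 40%, such as possibly poor sleep on the PSQI.
- State that the crash comparison, and any other outcome that proves similarly rare, will be reported as an estimate with a confidence interval and not as a powered test.

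The cost is one rewritten paragraph with less favourable figures. No extra participants and no change in trial conduct are needed.

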### Statistical plan

We plan to analyze anonymized data using an intention-to-treat approach (ITT). All outcome measures will be compared by assignment to the experimental and waitlist control groups in the primary analysis. The primary ITT analysis will include all participants who are randomized in the study. Secondary analyses will compare outcomes using an as-treated approach and an adherent to treatment approach. The as-treated approach will compare those who download dayzz to those who do not, regardless of their assigned randomization. We anticipate some cross-over between groups due to sharing of the app information among study participants. The adherent to treatment approach will exclude participants from the experimental group who did not engage with app throughout the study. We further plan to quantify temporal changes within participants assigned to the experimental group.

To evaluate changes in sleep behavior, we will examine the distribution of the data to determine if it meets assumptions for parametric tests. Assuming randomization has balanced known and unknown confounders and we observe a normal distribution, we will compare sleep duration between the groups using a t-test. We will use a rank sum test if the distribution is not normal. The distribution of the data will be examined, and transformations will be performed as necessary for valid comparisons. If potential confounders are not balanced between groups, we plan to use regression models with an appropriate link function and distribution to test all hypotheses. The number of healthy sleep changes at the end of the study will be compared between the groups using a rank sum test.

To evaluate changes in sleep quality, we will compare the proportion of participants with poor sleep quality according to the PSQI in the experimental group versus the waitlist control group using a chi-2 test. These continuous measures will be compared using a t-test. To examine changes in mood, alertness, and energy we will compare these ordinal variables using Wilcoxon rank sum tests between the experimental and waitlist control arms. We will estimate changes in absences and productivity using reported salary information and compare the cumulative cost of each using a t-test. We will estimate the incidence of crashes, near-crashes, and injuries which will then be compared using Poisson regression. Finally, we will compare cumulative healthcare costs over the study using t-tests.

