### Recruitment and retention

Recruitment will include two emails that will be sent to more than 20,000 members of the organization with an invitation to visit the study website for more information. An advertisement for the study will also be posted on a website hosted by the organization that is devoted to research and study recruitment, with a wide circulation (>10,000 visitors monthly). Finally, will post targeted social media advertisements to individuals who report the organization as their primary employer on Facebook and LinkedIn.

Potential participants will be directed to an online landing page with more information about the study. An online screener will be automatically scored and used to determine eligibility according to the study inclusion/exclusion criteria, resulting in either an invitation to provide consent and complete the baseline procedure, or a message indicating they were not eligible. Due to the virtual nature of this study, consent was collected via electronic signature. Participants were informed they could stop at any time, and who had questions were encouraged to email or call the study team. Participant responses will be de-identified and results published in aggregate. No identifiable data will be disclosed to the employer.

After providing consent via the online landing page, participants were automatically randomized by a computer program. Due to the multiple steps necessary to enroll in the experimental arm, we weighted assignment to the experimental group 1.3 to 1 to ensure equal enrollment in each group.

All enrolled participants will receive $25 for completing the baseline procedures, a t-shirt ($10 value) for completing the first monthly sleep diary, and a $20 gift card for completing the end-of-study questionnaire. Each month, participants who complete the monthly questionnaire which they receive via email will be entered in a raffle to win one of two pairs of Bluetooth wireless headphones ($250 value each). Finally, for each study component completed, participants receive chances for a raffle of gift cards, ranging in value from $100 to $500, at the end of the study. Participants who are unresponsive to emailed questionnaires will receive up to 2 reminder follow-up emails.

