### Study arms

#### Experimental arm

After consenting, participants randomized to the experimental group will take a short online initial contact questionnaire to collect basic demographics. They will then view a 20-minute sleep health education video. Immediately after the presentation, the participant will be presented with a short sleep disorders risk assessment which displays the results upon completion, either high risk for a sleep disorder (obstructive sleep apnea, insomnia, or restless legs syndrome) or low/no risk a sleep disorder. Participants are then presented with a baseline questionnaire to assess sleep, health, and lifestyle. Finally, the experimental group participants will be invited to download the study app (“dayzz”). They will be encouraged to use the dayzz app throughout the study (up to 9 months, depending on date of enrollment).

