#### Control

Participants assigned to the waitlist control condition will, at baseline, complete the same initial contact and baseline questionnaires. Participants in the waitlist control group will complete the eDiary and monthly and end-of-study questionnaires. At the end of the study, waitlist control participants will receive the intervention (SHAW and dayzz app).

Each participant will also complete a daily electronic sleep diary (eDiary) sent via email for one week within the first month of enrollment and for one week within the third month of the study. For up to 9 months following the baseline procedure, on the 28th of each month, each participant will receive an email with a link to the monthly questionnaire. At the end of the study, each participant will receive a link to complete the end-of-study questionnaire. The eDiary and all questionnaires are completed online. This study was approved by the Partners HealthCare Institutional Review Board (IRB) on February 10, 2020 (Protocol #: 2019P003277). Please see the Fig 2 for a flow chart describing the study procedures. Per the IRB, a Data Safety Monitoring Board was not required for this clinical trial.

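### The primary analysis is said to cover everyone randomised, but as written its t, rank-sum and chi-square tests compare only people with an observed outcome

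*Protocol article*

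**What the plan says.** The Statistical plan sets the primary population: "The primary ITT analysis will include all participants who are randomized in the study". It also sets the grouping: "All outcome measures will be compared by assignment to the experimental and waitlist control groups in the primary analysis". It then names the tests. For sleep duration, if the data look normal, "we will compare sleep duration between the groups using a t-test", with a rank-sum test otherwise. For behaviour, "The number of healthy sleep changes at the end of the study will be compared between the groups using a rank sum test". Poor sleep on the PSQI is compared "in the experimental group versus the waitlist control group using a chi-2 test". Mood, alertness and energy get rank-sum tests, cumulative costs get t-tests, and crashes, near-crashes and injuries get Poisson regression. Regression is otherwise a fallback for imbalanced confounders, not for missing data.

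The data come from self-report. The Control section, in text that covers both arms, says that for up to 9 months "on the 28th of each month, each participant will receive an email with a link to the monthly questionnaire". Recruitment and retention foresees non-response: "Participants who are unresponsive to emailed questionnaires will receive up to 2 reminder follow-up emails". The Power analysis is based on 1,000 people who remain active and supply usable data, 500 per arm, and gives a detectable effect of 0.16.

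**The concern.** The article fixes both a population and a set of tests, and as written the two do not match. A t, rank-sum or chi-square test needs one value per person. Without a stated step for absent values, anyone who did not return the form falls out, and the result is still labelled intention-to-treat on all randomised participants. The Power analysis describes a different and smaller set.

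What is at stake is bias, not only lost precision. Participants in a waitlist design know their arm, and only one arm is asked to keep using an app. If people who feel no benefit stop answering, and do so more in one arm, the remaining responders differ between arms even when the intervention does nothing. The trial is sized for a small effect, so a modest selection effect would matter.

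**Working it through.** **1. Outcomes, sources and tests (Measures, Control and Statistical plan sections)**

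| Outcome | Source | Named test | Person with missing data, as written |
|---|---|---|---|
| Sleep duration | eDiary weeks, months 1 and 3 | t or rank-sum | drops out |
| Healthy sleep changes | end-of-study form | rank-sum | drops out |
| Poor sleep (PSQI) | form not stated | chi-square | drops out |
| Mood, alertness, energy | eDiary and monthly forms | rank-sum, no time point named | drops out |
| Absence, productivity and healthcare cost | monthly forms, cumulated | t | drops out, or total understated |
| Crashes, near-crashes, injuries | monthly forms | Poisson | can contribute the months reported |

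**2. The plan's own target.** Detectable effect = (z_alpha + z_power) × √(2/n), with n = 500 per arm and √(2/500) = 0.0632. Alpha, sidedness and power are not stated.
- One-sided 5%, 80% power: (1.645 + 0.842) × 0.0632 = 0.157, which rounds to the stated 0.16.
- Two-sided 5%, 80% power: (1.960 + 0.842) × 0.0632 = 0.177.

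The unstated sidedness is a separate matter. Here 0.16 serves only as the yardstick.

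**3. Bias when only responders are compared, no true effect.** Let r be the response share in an arm and g the responder-minus-non-responder gap in SD (E experimental, C control). Then bias = (1 − rE)·gE − (1 − rC)·gC. The standard error is √(1/(500·rE) + 1/(500·rC)), and the test is two-sided 5%. All r and g values are assumptions.
- 80% v 80%, same gap: 0.20g − 0.20g = 0; false-positive rate 5%.
- 70% v 80%, gap 0.2: 0.06 − 0.04 = 0.02 SD; 5.9%.
- 70% v 80%, gap 0.5: 0.15 − 0.10 = 0.05 SD; 10.5%.
- 60% v 80%, gap 0.2: 0.08 − 0.04 = 0.04 SD; 8.2%.
- 60% v 80%, gap 0.5: 0.20 − 0.10 = 0.10 SD; 25.8%.
- 80% v 80%, gaps 0.5 v 0.2: 0.10 − 0.04 = 0.06 SD; 13.6%.

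The last line shows that equal response rates are not enough if selection differs by arm.

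**4. Repeated monthly data.** A simulation used 500 per arm, six monthly normal values with correlation 0.6, no true effect and 3,000 trials per scenario. Drop-out depended on the last reported value, with log-odds per SD of 0.3–0.4 in the experimental arm and 0–0.3 in controls.
- With 61–67% v 76% answering the last form, the responders-only test was biased by 0.02–0.09 SD, with a false-positive rate of 6–24%.
- With 72% in both arms and log-odds 0.3 v 0.1, the bias was 0.04 SD and the rate 9%.
- A repeated-measures model on all returns had bias of 0.002 SD or less, about a 5% error rate, and a standard error of about 0.070 against 0.075, roughly 7% smaller.

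The near-zero bias is largely built in: drop-out depended on reported values, and the model was given the true covariance. If drop-out depends on unreported values, the model removes only part of the bias.

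**5. Cumulative costs.** Suppose each person has the same true monthly cost and missed months count as zero. If the arms return 60% and 80% of forms (assumed), recorded totals stand in the ratio 0.60/0.80 = 0.75, so one arm looks 25% cheaper with no true difference. Excluding people with any missed month avoids this but gives up the stated population.

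**6. Randomised against enrolled.** Randomisation follows consent and is weighted 1.3 to 1 so that enrolment comes out equal. If the control arm loses nobody, 500 enrolled per arm implies 650 + 500 = 1,150 randomised, so 150 (13%) would never enrol. They are within the stated population but outside the Power analysis set.

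**The case against.** The strongest reply is that this is a condensed article with no analysis plan shown, and that missing-data handling is commonly left to that plan. A reader might infer that these tests can use only returned forms, and hence that the primary result must be a responders-only comparison. The documents do not support that: all three tests can be run on imputed data and pooled, and the full plan may say so. In context, the all-randomised sentence is also set against the as-treated and adherent analyses, so it may mean chiefly that nobody is removed for crossover or non-use.

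A reader might also infer that bias will arise and favour the app. That too is unsupported. Both arms get the same questionnaire emails and incentives, and reminders are not described as differing by arm. App prompts could as easily raise experimental-arm response. Every unequal scenario above assumes worse retention or stronger selection in the experimental arm, so the direction follows from the assumption. The simulation also uses a normal outcome at a last monthly wave, which is not how diary sleep duration or ordinal mood is measured.

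These points stand, and they limit the claim. They do not remove the mismatch: the article states a population, the named methods do not deliver it as written, and the Power analysis uses another set.

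**Conclusion.** The point holds as a mismatch between the stated population and the stated analysis, and it should be corrected before the data are analysed. It affects the t, rank-sum and chi-square comparisons and the cumulative costs, but not the Poisson outcomes in the same way. Bias follows only if response, or its relation to outcome, differs by arm. The documents give no response rate, responder gap or within-person correlation, so 0.02–0.10 SD against 0.16 illustrates what 60–70% v 76–80% response could do under assumed selection. It is not an estimate for this trial.

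**What to change.** - **Repeated monthly outcomes** (mood, alertness, energy, absence, performance, costs): make the primary analysis a mixed model of a type suited to each outcome, on all returns by month since randomisation, with arm, month and arm-by-month. Report the arm difference averaged over follow-up, or at a prespecified month that every participant can reach. The last month will not serve, because follow-up length depends on enrolment date.
- **Outcomes measured once or twice** (diary weeks, end-of-study items): use multiple imputation by arm from the initial-contact data and any available returns. Experimental participants "will take a short online initial contact questionnaire to collect basic demographics" before the education video, and controls complete the same form. The experimental arm's baseline questionnaire comes after the video, so it is a poorer source. The PSQI goes with whichever group matches its schedule.
- **Sensitivity and reporting:** add one delta-adjusted analysis, and show response by arm and month.
- **Randomised but never enrolled:** these people have no follow-up returns, and those who left before the initial-contact form have nothing to impute from. Count and report them by arm.
- **If the simple tests stay primary:** change the population sentence to *all randomised participants who provided the outcome, analysed as assigned*, and reconcile it with the Power analysis.

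The cost is wording and modest programming, with no new data or participants. The downside is reliance on missing at random, which the delta-adjusted analysis probes.
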